## Abstract

**Introduction:**

Hookworm infection is a leading cause of iron deficiency anemia and malnutrition in resource-poor settings. Periodic mass deworming with anthelminthic drugs remains the cornerstone of hookworm control efforts worldwide. Reinfection following treatment occurs, reflecting the human host's inability to acquire immunity following exposure to an untreated reservoir of infection. This cluster randomized trial will evaluate the effectiveness of a modified, population-based, mass deworming strategy in reducing hookworm infection in an endemic southern Indian population.

**Methods:**

Forty five tribal villages were randomized into three groups: one received annual treatment; the second received two rounds of treatment at 1-month intervals; and the third received four rounds of treatment – two rounds 1 month apart at the beginning, followed by another two after 6 months. Stool samples collected through cross-sectional parasitological surveys pre- and post-intervention, and at 3-monthly intervals for a period of 1 year were tested for presence of hookworm ova. Long-term effectiveness of treatment will be assessed through another survey conducted 2 years after the last treatment cycle.

**Results:**

From a population of 11,857 individuals, 8681 (73.2%) were found to be eligible and consented to participate, out-migration being the primary reason for non-participation. Baseline stool samples were obtained from 2082 participants, with 18.5% having hookworm infection, although majority were low intensity infections (<2000 eggs per gram of feces).

**Discussion:**

This study will help identify the optimal mass deworming strategy that can achieve the greatest impact in the shortest period of time, particularly in settings where long-term program sustainability is a challenge.

## Introduction

1

Hookworms, along with the other soil transmitted helminths (STH), *Ascaris lumbricoides* and *Trichuris trichuira*, are among the commonest gastrointestinal infections in humans [1]. Hookworms affect an estimated 438.9 million people worldwide, resulting in 3.2 million disability adjusted life years (DALY) [2]. This exceeds the disability burden of most other tropical diseases [3], [4]. Most human hookworm infections are caused by two species - *Necator americanus* and *Ancylostoma duodenale*, although considerable regional variation in the species composition has been described [5]. There is a clear relationship between hookworm prevalence and low socioeconomic status, with the majority of “at risk” population living on less than US$2 per day [6], [7].

In children, hookworm infections are associated with iron-deficiency anemia, stunted growth, poor nutritional status and reduced physical and cognitive abilities, and therefore may profoundly impact school performance and future economic productivity [8], [9]. Increasing hookworm infection intensity is also associated with lower hemoglobin levels in adults, particularly in pregnant women living in low-income countries [10], [11].

The World Health Organization (WHO) has set a global target of regularly treating at least 75% of the pre-school and school-aged children in endemic areas through school-based deworming programs to eliminate morbidity due to STH by 2020 [12]. Despite high cure rates [13], [14], failure to prevent reinfection even after effective treatment is a recognized shortcoming of this strategy [15], [16], [17], [18], often due to an untreated reservoir of infective stages in the environment. In a meta-analysis, a 30% reinfection rate was observed at 3 months post-treatment, increasing to 57% at 12 months [19]. A positive correlation between pre-treatment infection intensity and reinfection status has also been noted [18]. Moreover, recent modeling-based estimates suggest that school-based deworming may have limited impact in interrupting the community transmission of STH infections, especially in places where hookworm predominates because most infection is harbored by adults [20]. The transmission of an infectious agent following drug treatment is a dynamic process, and is determined by many factors including treatment frequency, coverage and efficacy [21], [22]. Suboptimal treatment may result in persistence of an untreated reservoir of transmission, thereby increasing the likelihood of reinfection [23] and the need for periodic treatments to interrupt transmission in endemic communities [24]. This, in turn, raises the question of long-term sustainability of such programs and the possibility of emergence and spread of drug resistance [25], [26]. There is a need for studies comparing different regimens of mass drug administration (MDA) against hookworm infection to identify optimal deworming strategies that can minimize morbidity or interrupt transmission, thereby enabling the MDA to be stopped.

The primary objective of this study is to compare the hookworm reinfection rates between a population-based MDA strategy of an annual treatment cycle (with albendazole) with two and four cycles of treatment respectively, for a period of 1 year in an endemic tribal population in southern India [27]. The secondary objective is to identify individual, household, community and spatial correlates of infection; and to develop predictive models to understand the dynamics of hookworm transmission in endemic populations. The highly aggregated nature of worm distribution within human communities and predisposition to reinfection among those heavily infected is well established [20], [28].

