### Outcome measures

2.4

The effectiveness of treatment was evaluated qualitatively, based on the prevalence of hookworm infection, and quantitatively based on the intensity of infection (fecal egg count). Prevalence and intensity of infection at the end of 12 months after the last MDA cycle is the primary outcome measure for this study. Secondary outcome measures include prevalence and intensity of infection after each treatment cycle and at 3, 6, and 9 months post-treatment. Long-term effectiveness of the treatment on prevalence and intensity of infection will be assessed through a follow-up cross-sectional parasitological survey 2 years after the last MDA cycle.

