### Sample size

2.5

The sample size was calculated based on following assumptions: 38% prevalence of hookworm infection at baseline [27]; CR of 75% [14]; reinfection rate of 60% at the end of 1 year [19] in the single cycle group; a minimum effect size of 30%; power of 80%; alpha error of 5%; and 10% refusal rate. This requires approximately 165 participants in each group [32]. Since this is a cluster randomized trial, the sample size was inflated to account for the increased variance due to clustering of hookworm cases at village and household levels [33]. Analysis of data from two previous cross-sectional studies in Tamil Nadu [27], [34] showed an intra-cluster correlation coefficient of 0.06 for hookworm infection, which translated into a design effect of 2.7 for a cluster-size of 30. Based on this, a total sample size of 450 participants per intervention group (single/two/four cycles) was considered adequate to detect effectiveness of the intervention regimes, both qualitatively and quantitatively. Thus, at least 1350 participants in 45 clusters (30 in each cluster) had to be contacted during each parasitological survey (Fig. 2).

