### Baseline data collection and follow-up

2.7

Detailed information on socio-demographic and hygiene characteristics were collected from all participants at baseline through a door-to-door survey of the households. Stool samples from a subset of participants were collected at baseline, after each round of MDA, and at 3-monthly intervals until the end of 1 year. A follow-up survey will be conducted at the end of 2 years after the last MDA cycle to assess long-term effectiveness of the treatment. The stool sample collection schedule (including the planned follow-up parasitological survey) is presented in Fig. 2. Because of the seasonal migration pattern of the study population, the parasitological surveys (pre-MDA/post-MDA/follow-up) were conducted as separate cross-sectional studies.

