### Statistical analysis

2.10

All variables will be examined using descriptive statistics (measures of central tendency [means and medians], dispersion [standard deviations, interquartile ranges]) for continuous variables, frequency counts and marginal percentages [with 95% confidence intervals] for categorical variables). The success of randomization will be evaluated by comparing the baseline characteristics between the treatment and control groups; no formal statistical testing will be performed as per the CONSORT (Consolidated Standards of Reporting Trials) recommendation [39]. The primary analysis will be an intention-to-treat analysis comparing prevalence and intensity of infection between the three groups at the end of 12 months after the last MDA cycle, adjusted for age and gender. Generalized estimating equations (GEE) will be used to account for the correlated data structure [40]. The prognostic effect of variable(s) with noticeable baseline imbalances will be assessed by comparing results of analysis with and without adjustment for such variable(s) [41]. The effect of clustering at village and household levels will be explored through multilevel (hierarchical) modeling [42]. In all analyses, past research demonstrates much variability in fecal egg counts (negative binomial distribution); this will be accounted for where appropriate.

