### Mathematical model building

2.11

Mathematical models have extensively been used to understand the dynamics of helminth transmission and to investigate the effectiveness of MDA in controlling infection [43], [44], [45]. When backed by robust field data, they have great potential to enhance the design, and hence effectiveness, of disease and infection control programs.

The data collected from this study (pre- and post-treatment fecal egg count, prevalence of hookworm infection, and per capita reinfection rates in the age and gender groups within the treatment groups) will provide the key parameters to build the hookworm transmission models. The effect of different MDA regimes on hookworm transmission will first be assessed using established deterministic age-structured models [46] and individual-based stochastic models [47]. The complex host-parasite interaction on transmission and drug efficacy at the individual, household and community level will then be explored using simulation techniques based on the stochastic model. Particular attention will be given to the impact of migration for temporary employment, and individual compliance over multiple treatment events.

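### The objective, sample size and one model input are reinfection rates, but the surveys and primary analysis give only prevalence and intensity, which can fall with more cycles even if reinfection is unchanged

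*Protocol article*

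**What the plan says.** **Where reinfection is the target.** The Introduction states: "The primary objective of this study is to compare the hookworm reinfection rates between a population-based MDA strategy". Section 2.5 (Sample size) takes as separate inputs "38% prevalence of hookworm infection at baseline", a 75% cure rate, a 60% one-year reinfection rate in the single-cycle group and a 30% minimum effect. Section 2.11 (Mathematical model building) lists among the data the study will supply "per capita reinfection rates in the age and gender groups within the treatment groups".

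**Where prevalence and intensity are the target.** Section 2.4 (Outcome measures): "Prevalence and intensity of infection at the end of 12 months after the last MDA cycle is the primary outcome measure for this study". Section 2.10 (Statistical analysis): "The primary analysis will be an intention-to-treat analysis comparing prevalence and intensity of infection between the three groups".

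**How the data arise.** Section 2.7: "Stool samples from a subset of participants were collected at baseline, after each round of MDA, and at 3-monthly intervals". The same section adds that, because of seasonal migration, "the parasitological surveys (pre-MDA/post-MDA/follow-up) were conducted as separate cross-sectional studies". The article defines no reinfection outcome and describes no follow-up of people shown to be clear of infection.

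**The concern.** A reinfection rate needs a person known to have been infected, known to have cleared, and then examined again. A cross-sectional survey at 12 months gives the share infected at that time. That share mixes four groups: people reinfected after cure, people never cured, people newly infected, and people whom treatment missed.

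The arms differ in number of doses, so the share never cured can differ by arm by design. A lower 12-month prevalence in the two- or four-cycle arm would then show that the strategy leaves fewer people infected, but not by which route. Fewer residual infections and slower reacquisition have different implications for a programme that hopes to stop treatment, and they enter a transmission model as different parameters. At stake are the wording of the main conclusion, the meaning of the sample size, and one model input.

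**Working it through.** **1. The plan's sample size.** Inputs from section 2.5: baseline prevalence 38%, cure 75%, reinfection 60%, effect 30%, power 80%, alpha 5%, refusal 10%. I read the effect as 30 points and alpha as two-sided; the article states neither.
- 60% against 30%, pooled two-proportion formula: 42 per arm.
- Scale up to all participants, because only cured positives count: 42/(0.38 × 0.75) = 147.
- Allow for refusal: 147.4/0.90 = 164, against approximately 165 stated.
- Design effect: 1 + 29 × 0.06 = 2.74; 165 × 2.74 = 452, against 450 stated.

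This reading uses every stated input. A 30% relative effect (60% against 42%) needs 120 cured people per arm, and the same scaling gives 120/0.285/0.90 = 468. It comes near 165 only if the 38% and 75% are left out and alpha is split over two comparisons (about 146/0.90 = 163), which the article does not state.

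**2. Prevalence when reinfection is the same in every arm.** Let u be the share of baseline infections still uncured after treatment and r the reinfection risk. Then 12-month prevalence = 0.38 × [u + (1 − u) × r]. Assumptions: each dose cures 75% independently, everyone is treated, and nobody uninfected at baseline becomes infected.
- One cycle, u = 0.25: 0.38 × (0.25 + 0.75 × 0.60) = 26.6%.
- Two cycles, u = 0.0625: 0.38 × (0.0625 + 0.9375 × 0.60) = 23.75%, a relative fall of 10.7%.
- Four cycles, with 30–57% of the cleared reinfected before the third cycle (the 3- and 12-month figures in the Introduction, taken as a range): 23.1–23.4%, a fall of 12–13%.

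**3. Comparison with the planned effect.** Reinfection cut from 60% to 30% with cure unchanged: 0.38 × (0.25 + 0.75 × 0.30) = 18.05%, a 32% fall from 26.6%. The two-cycle cure-only fall is 10.7/32.1, or one third of that.

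**4. Sensitivity of the 10.7%.**

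| Change in assumption | Two-cycle fall, reinfection unchanged |
|---|---|
| Second dose cures 0 / 25 / 50 / 75% of those left infected | 0 / 3.6 / 7.1 / 10.7% |
| 10–20% of the uninfected 62% acquire infection | 8.7–7.3% |
| 73.2% treated (enrolled share), the rest stay at 38% | 7.0% |
| Reinfection 30% instead of 60% in every arm | 27.6% |

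At the observed 18.5% baseline, prevalence is 13.0% against 11.6%, the same 10.7% relative fall.

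**5. Could linkage supply reinfection rates?** Results report 386 positives among 2082 sampled, from 8681 enrolled. Expected cured positives: 386 × 0.75 = 290 in the whole trial, about 97 per arm. If each subset is redrawn independently (an assumption), the number per arm seen again at 12 months is:
- at the baseline share, 2082/8681 = 24%: 97 × 0.24 = 23;
- at the planned minimum, 1350/8681 = 15.6%: 15.

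Reaching the 42 needed before clustering would take 42/96.5 = 44% resampled. Documented clearance would also require a post-cycle sample from the same person.

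**6. What 450 per arm delivers for prevalence.** Effective size is 450/2.74 = 164 per arm (two-sided 5%, one comparison, all 450 analysed).
- Planned reinfection effect with equal cure, 26.6% against 18.05%: 372 per arm before clustering, 372 × 2.74 = 1,019 after; power with 450 is about 46%.
- Same effect plus two-dose cure, 26.6% against 0.38 × (0.0625 + 0.9375 × 0.30) = 13.1%: power about 87%.

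Power on the scale actually analysed therefore depends heavily on the mechanism that prevalence cannot identify.

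**The case against.** **Prevalence is the right measure for a strategy trial.** The Abstract, section 2.4 and the Discussion speak of infection and effectiveness, and section 2.2 presents higher coverage and lower worm intensity as intended effects of more cycles. This stands. A reader might infer that the primary comparison is biased or uninformative; the documents do not support that. Randomisation protects the comparison of 12-month prevalence and intensity between strategies.

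**The cure-only fall is near the top of its range at 60% reinfection.** This also stands. Independent cure, full coverage and no new infection all push it up, and it could be zero if the second dose clears nobody left infected. Lower reinfection pushes it the other way. A reader might infer that any observed difference would be due to cure alone; the figures show only that part of it can arise with reinfection unchanged.

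**The surveys after each cycle and at 3, 6 and 9 months separate early clearance from later rise.** They do so partly, for groups. The later rise still includes new infections and untreated people, so it is not a reinfection rate among the cured.

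**The resampling count is hypothetical.** Agreed: section 2.7 does not say how subsets are drawn, and overlap could be larger. The article nonetheless describes the surveys as separate and plans no linked analysis.

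**The investigators may never describe the result as reduced reinfection.** True; the article does not say they will. The stated primary objective invites it.

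**Conclusion.** The mismatch is established from the text alone: the primary objective, and an input promised to the models, are quantities that the described surveys do not measure. The sample size supports this, since the reading that uses all stated inputs is a comparison of reinfection among cured positives. That reconstruction is close (164 against about 165) but remains an inference, because the article does not say whether the 30% is absolute or relative.

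The size of the mixing is moderate. On the plan's figures and independent cure per dose, two cycles lower 12-month prevalence by 10.7% in relative terms with reinfection unchanged, about a third of what the planned reinfection effect would produce, and four cycles by 12–13%. The plausible range runs from zero to 10.7% at 60% reinfection, and higher if reinfection is lower.

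It would go too far to say that reinfection cannot be studied at all: people sampled more than once could inform it, though under independent redrawing at 24% that is about 23 of 97 per arm, too few for the planned comparison. This should be corrected before results are reported. It does not undermine the trial's value as a comparison of strategies.

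**What to change.** 1. **Objective and conclusion.** Restate the primary objective as comparing prevalence and intensity of hookworm infection 12 months after the last cycle. Do not report between-arm differences as reduced reinfection.
2. **Sample size.** State that 165 and 450 per group were derived for reinfection, say whether the 30% effect is absolute or relative, and give what 450 delivers for prevalence under stated cure and reinfection assumptions.
3. **Descriptive secondary measure from surveys already planned.** By arm, report the early post-cycle prevalence and the later rise to 12 months, with intervals that respect village clustering. For the four-cycle arm, fix in advance which post-cycle survey (after month 2 or after month 9) is the reference. Label it a group-level measure and not a reinfection rate.
4. **Linked data.** Report reinfection only in people whose identifiers show that they were actually resampled, with their number.
5. **Section 2.11.** Do not pass survey prevalence, or its rise, to the transmission models as a per capita reinfection rate.

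No new data collection is needed. The cost is a narrower headline claim, some rewording and a small additional analysis.

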## Materials and methods

2

### Study setting

2.1

This ongoing study is being conducted in the Jawadhu Hills (JH) block, at the borders of Vellore and Tiruvannamalai districts of Tamil Nadu in southern India (Fig. 1), with a population of about 80,000, mostly tribal with a common ancestry. It has 11 panchayats with about 250 villages; each village has between 15 and 100 households. The community is predominantly agrarian, cultivating rice, millet and maize; pig rearing is a common practice. During non-agricultural seasons, many people migrate to coffee plantations in the neighboring states as short-term (temporary) laborers.

**Fig. 1 fig1:**
[figure not shown]
Map showing location of the study area.

The area has a hilly terrain with poor road access, lack of safe drinking water and poor sanitation facilities. It is endemic for lymphatic filariasis, and all residents aged >1 year are under a mass treatment program with annual co-administration of diethylcarbamazine (DEC) and albendazole since 2007, as part of the Government of India (GoI) initiative to eliminate lymphatic filariasis [29]. Despite this, a cluster survey of 1237 subjects from 680 households in 2011 found a very high hookworm burden, with an overall prevalence of 38%. As is typical for hookworm infection, the prevalence and intensity of infection increased with age [27].

### Study design

2.2

The study is an open-label, cluster randomized, community-intervention trial. A total of 45 villages (clusters) with similar population structure, water supply and sanitation practices were selected. The villages were randomized into one of three groups (Fig. 2):1.Single cycle (15 villages): Village residents of all ages in this group received only one cycle of 400 mg albendazole, at month 1.2.Two cycles (15 villages): Village residents of all ages in this group received two cycles of 400 mg albendazole at 1 month interval, at month 1 and 2.3.Four cycles (15 villages): Village residents of all ages in this group received two cycles of 400 mg albendazole at month 1 and 2, followed by another two cycles at month 8 and 9 (a total of four cycles).

**Fig. 2 fig2:**
[figure not shown]
Schematic diagram representing the timelines for mass drug administration (MDA) and stool sample collection in the three intervention groups. The black dots represent the number of stool samples collected per participant at each time point. The stool samples are collected through multiple cross-sectional parasitological surveys. The dashed line represents the time elapsed between the primary data collection and the follow-up survey.

The timing of the MDA cycles in the 2- and 4-cycle groups is based on the hookworm biology. The released rhabditiform larvae take about 5–10 days in the soil to become the infective filariform (third-stage) larvae [30]. Hence, it was hypothesized that a second MDA cycle (in the 2-cycle group) covering the extrinsic incubation period will reduce reinfection from the infective larvae already present in the soil. However, as the larvae are known to survive in soil for weeks under favorable environmental conditions [31], it was speculated that these two treatment cycles may not be adequate to achieve transmission breakpoint in endemic settings; therefore another intervention group (the 4-cycle group) with two additional MDA cycles after 6 months was added (Fig. 2). Moreover, multiple treatment cycles will result in an overall increase in MDA coverage and a subsequent reduction in worm intensity, thereby reducing the need for repeated treatments.

